#### Sample-size calculations

To determine the appropriate sample size for this trial, the following factors were considered: (1) the primary and secondary outcomes in the trial, (2) clinically significant differences for the outcomes based on our previous RCT, (3) Type I (alpha) and Type II (beta) errors, (4) estimates of variation from our pilot data, (5) study design, and (6) dropouts. These calculations represent sample size for the overall comparisons between the four professional groups and two intervention groups. Sample-size estimation was based on detecting an effect size of 0.40 between groups on any of the three aspects of outcome (usability, usefulness, and knowledge/attitude/behavior). Assuming Type I error = 0.05 (two-tailed), Type II error = 0.80, and the effect size = 0.40, the sample size required per group is 80. The sample size required for two comparison groups across four professions = 80 × 2 × 4 = 640. To account for our dropout rate (8/431), we have conservatively added 30 to recruit a sample of 670 practitioners. For analysis of response mediators, an *R*^2^ of 30% corresponds to an effect size of 0.42; 600 practitioners provides more than 99% power to detect this effect size with 12 predictors [79].

This study is organized locally but recruits participants internationally to inform practitioners of the study and the potential for free access to evidence resources. Our multimodal recruitment strategy will use professional associations, websites/conferences, and social media to inform practitioners of the study and the potential for free access to evidence resources.

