We also plan to analyze difference in professional attitudes, evidence access, and use. We have powered our study to allow this analysis. Our subgroup analyses will also describe differences in types of evidence accessed. Our group previously determined that physicians prefer systematic reviews to primacy studies and that access was better through peer-reviewed journals than through Cochrane Collaboration [83]; we will now extend this type of analysis to look at evidence accessed across professions by comparing the types of primary studies (clinical, basic science; quantitative/qualitative), content (prognosis, diagnosis, clinical measurement, treatment effectiveness/outcomes, economic, etiology), and journals (disciplinary/interdisciplinary/other discipline).

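### The stated two-tailed inputs need 99 to 100 participants per group, not 80, and the power is labelled as Type II error

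*Protocol article*

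**What the plan says.** The Sample-size calculations section sets the target effect: "Sample-size estimation was based on detecting an effect size of 0.40 between groups on any of the three aspects of outcome". It then gives a two-tailed Type I error of 0.05 and concludes: "Type II error = 0.80, and the effect size = 0.40, the sample size required per group is 80".

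That figure is multiplied up: "The sample size required for two comparison groups across four professions = 80 × 2 × 4 = 640". Dropout is handled by a flat addition: "To account for our dropout rate (8/431), we have conservatively added 30 to recruit a sample of 670 practitioners". The section describes the purpose as follows: "These calculations represent sample size for the overall comparisons between the four professional groups and two intervention groups".

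Study design and pilot estimates of variation are listed among the factors considered. However, the printed calculation contains no within-person correlation, baseline adjustment or crossover term. Elsewhere, Methods/design describes a two-period crossover in which every participant receives both forms of access, and Planned data analyses specifies mixed-effects models for repeated measurements.

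**The concern.** The section prints every input to a two-group comparison of means and then a result that those inputs do not give. It also assigns the value 0.80 to the Type II error, where only power makes sense.

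The enrolment target is built directly on the figure of 80. A reader who takes the paragraph at face value will believe that a comparison of 80 with 80 has 80% power for a standardised difference of 0.40, and will interpret a null result within one profession accordingly. If the analysis falls back on comparing the two arms within a profession in the first period, the real power is lower than that reader assumes. Methods/design itself names incomplete wash-out as the design's main drawback and plans a test for order effects, so this fallback is not far-fetched.

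**Working it through.** **Inputs, all from Sample-size calculations:** alpha 0.05, two-tailed; 0.80, read as power (Type II error 0.20); standardised difference d = 0.40 between groups; 80 per group; 2 arms × 4 professions; dropout 8/431 = 1.86%.

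**1. Trying to reproduce 80.**

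n per group = 2(z₁₋α/₂ + z₁₋β)² / d²

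- Two-tailed 5%, power 0.80: 2(1.960 + 0.842)² / 0.16 = 98.1, so 99. The t-test version gives 99.08, so 100.
- One-sided 5%, power 0.80: 2(1.645 + 0.842)² / 0.16 = 77.3, so 78 (t-test 77.97, also 78). This is close to 80, but the text says two-tailed.
- Type II error of 0.80 taken literally (power 0.20): 2(1.960 − 0.842)² / 0.16 = 15.6, so 16.
- Paired test with 0.40 as the standardised within-person difference: about 51 to 52 participants.

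None of the two-sided calculations tried gives 80 from the printed inputs alone.

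**2. Total implied by the stated inputs.**

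| | 99 per cell | 100 per cell | Protocol (80) |
|---|---|---|---|
| × 8 cells | 792 | 800 | 640 |
| ÷ (1 − 8/431) | 807 | 816 | 653 |
| or flat + 30 | 822 | 830 | 670 |

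**3. Power of 80 against 80 as a parallel comparison within one profession.**

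SE = √(2/80) = 0.158 SD; 0.40/0.158 = 2.530; power = Φ(2.530 − 1.960) = Φ(0.570) = 71.6%. The t-test gives 71.0%. The difference detectable with 80% power is 0.446. If all 670 recruits are retained (670/8 = 83.75 per cell), power is 73.0% (t) to 73.5% (normal).

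**4. Where the 71% does not apply.**

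*Crossover contrast within a profession.* All 160 participants receive both conditions. With no carryover, SE = √(2(1 − ρ)/160). The within-person correlation ρ is not in the document, so a range is shown.

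| ρ (assumed) | SE (SD units) | Power for 0.40 |
|---|---|---|
| 0 | 0.112 | 94.7% |
| 0.3 | 0.094 | 99.0% |
| 0.5 | 0.079 | 99.9% |

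*Pooled comparison of arms, 320 against 320.* SE = √(2/320) = 0.079; power 99.9%; detectable difference about 0.22.

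*Profession against profession, 160 against 160.* Power is 94.7% unadjusted (94.6% by t-test), and 82.6% with a Bonferroni correction for six pairs.

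**The case against.** The strongest reply is that the error has little practical effect. Participants act as their own controls, the mixed model uses that dependence, and each profession contributes about 160 people to the PUSH versus PULL contrast. Even at zero correlation the power is about 95%, provided there is no carryover. Sizing a crossover as though it were a parallel trial is conservative when carryover is absent, and it gives some protection if only the first period can be used. This stands, and it limits the consequence of the error.

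A second reply is that the route to 80 may rest on something not printed, since the section mentions pilot variation and study design. Baseline adjustment multiplies the requirement by (1 − ρ²), and 98.1(1 − ρ²) = 80 when ρ is about 0.43. That is possible, but neither the correlation nor the adjustment is given. As printed, the result still does not follow from the inputs.

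A reader might also infer that the statement in Planned data analyses, "We have powered our study to allow this analysis", is refuted. It is not. That sentence refers to differences between professions, which compare about 160 with 160 and keep more than 80% power for 0.40 even after the Bonferroni correction shown.

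**Conclusion.** The point holds as an error in the printed calculation. Two-tailed 5%, 80% power and a difference of 0.40 require 99 to 100 per group, about a quarter more than 80, and 792 to 800 in total before dropout. The value 0.80 is power, not Type II error.

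The loss of power is real but narrow: about 71% instead of 80%, for a first-period or single-time-point comparison of the two arms within one profession. It would matter if, for example, carryover prevented use of both periods.

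A reader might infer that the trial, or all its profession-level comparisons, are underpowered. The document does not support that. The crossover contrast within a profession, the pooled comparison and the unadjusted comparison of two professions each have about 95% power or more for 0.40. The crossover figure assumes no carryover, and any gain above 95% depends on a within-person correlation that the document does not state. All these figures assume equal cells of 80.

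**What to change.** Keep the target of 670 and rewrite the paragraph:

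- Give the error rates as Type II error = 0.20 (power 0.80).
- Remove the claim that 80 per group is what the inputs require. State instead that 80 per arm per profession gives about 71% power for 0.40, and 80% for about 0.45, in a parallel two-sided comparison within one profession, and that the pooled comparison of 320 per arm has over 99%.
- If 80% or more is to be claimed for the PUSH versus PULL effect within a profession, derive it from the crossover contrast. State the within-person correlation, preferably from the pilot data, and the no-carryover assumption. For orientation, power is about 95% at correlation 0 and 99% at an assumed 0.3.
- If 80 came from a baseline-adjusted calculation, state the adjustment and the correlation used.

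The cost is new wording and one recalculation. No participants are added and no analysis changes. One stated power becomes less favourable. The protocol article reports enrolment at just over 70% of target, so the restatement could be made before the analysis.

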## Methods/design

The trial is a crossover randomized controlled trial (RCT) with repeated baseline and follow-up measurements (Figure 1). The interventions are two different types of access to pain research evidence for four different types of professionals involved in pain management. The trial will begin with a three-month (repeated) baseline, during which average participant use of the standard PULL resource will be monitored. Participants will then be randomly allocated to either receive PUSH + PULL or continue to use the PULL resource. After six months, participants will cross over to the alternate intervention for an additional six months. To complete the trial, both groups will finish with three months of PUSH + PULL access. The repeated baseline period provides more stable estimates of participants’ access prior to randomization. The rationale for the crossover design is that it will maximize our statistical efficiency, increasing the precision of effect estimates. This is particularly important for our subgroup (profession) estimates; it will also provide better control of unknown potential confounders. The main potential drawback of a crossover design occurs if the “wash-out” is incomplete. While we will have control of the intervention delivery, the exposure to email alerts may affect use of the pull resources; therefore, we will test for order effects. The study received Ethics Approval from the McMaster University Research Ethics Board.

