#### Planned data analyses

Quality checking of primary and secondary outcome data will be performed by re-entry of 100 cases and checking concordance. Descriptive statistics, including frequencies, means, and standard deviations, will be calculated and data displayed graphically for all study variables as a means of exploring data distributions. The data for all outcome measures will be analyzed to ensure that they meet the statistical assumptions necessary to use parametric statistics. Transformations may be considered if necessary to meet test assumptions. To test our main research question, we will use general, linear mixed-effects models [82] for repeated measurements over time to explore the relationship among the use/behavior scores, comparing the effects between professional groups and intervention types. The models will be fitted for the outcome scores over time as a function of the between-participant (profession/intervention) and within-participant (time) variables. Utilizing a mixed-model approach allows us to account for the dependence between outcome measurements taken over time from the same participant. The structure of the variance-covariance matrix, which dictates the dependence between measurements in the fitting of the model, will be chosen based on standard criteria in statistics. *Post hoc* pairwise comparisons of the two treatment arms at different time points will be done using multiple comparisons with adjustment to the Type I error rate. Type I error will be set to 5% (*i.e.*, α = 0.05) for all the calculation of the confidence intervals and performing the various hypothesis-testing procedures. Type I error will be adjusted accordingly for multiple comparisons. Standard diagnostic tools will be used to assess any of the model fittings. An intent-to-treat analysis will be employed—those who do not participate will be included in the analysis in their original group. No interim analyses are planned since there are no safety issues and we wish to ensure full power for both primary and secondary analyses.

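### The PUSH + PULL versus PULL comparison is sized as two independent groups of 80 per profession, so the stated figures are not those of the crossover; the error is conservative

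*Protocol article*

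**What the plan says.** The Sample-size calculations section lists the study design among the factors considered. It then sets the target: "Sample-size estimation was based on detecting an effect size of 0.40 between groups on any of the three aspects of outcome". The inputs and the result stand in one sentence: "Assuming Type I error = 0.05 (two-tailed), Type II error = 0.80, and the effect size = 0.40, the sample size required per group is 80". The total follows by multiplication: "The sample size required for two comparison groups across four professions = 80 × 2 × 4 = 640". That is 160 per profession, 80 for each intervention. No within-participant correlation and no SD of a within-participant difference enters, and the section does not say that ignoring the crossover was a deliberate safety margin.

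Methods/design describes a different structure: "After six months, participants will cross over to the alternate intervention for an additional six months". Randomization makes the switch automatic at nine months. The reason for the design is also given: "The rationale for the crossover design is that it will maximize our statistical efficiency, increasing the precision of effect estimates". The text adds that this matters most for the profession subgroups. Planned data analyses relies on the same feature: "Utilizing a mixed-model approach allows us to account for the dependence between outcome measurements taken over time from the same participant".

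**The concern.** Multiplying by two interventions counts each clinician under one condition only. In this trial all 160 clinicians in a profession supply data under both, so the PUSH + PULL versus PULL contrast can be formed within persons. The variance of that contrast depends on the within-participant correlation, which the calculation never uses. The article thus chooses the crossover for its precision and then sizes the trial as if that precision did not exist.

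What is at stake is the meaning of the stated power and detectable effect. A null result read against 0.40 would understate how small an effect the trial could have excluded in each profession. The article also says that it is powered for professional differences, but it gives no power for a difference between professions in the response to PUSH.

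**Working it through.** **Inputs from the article.** Two-sided alpha 0.05; standardised effect 0.40; 80 per group; 2 × 80 = 160 per profession; all participants cross over. Power is taken as 0.80. The article prints "Type II error = 0.80", and the literal reading (power 0.20) would need only 16 per group, so 80% power is the only sensible reading.

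**Assumptions.** The effect is in units of the SD of a single score (SD = 1). Each profession is split equally between sequences. The contrast is within-participant and adjusted for period, with no carryover. The article gives no rho, so a range of 0 to 0.8 is used.

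**Step 1: the article's own figure.** For two independent groups, n = 2 × [(1.960 + 0.842)/0.40]² = 98.1, so 99 per group. The stated 80 is not reproduced; a one-sided test gives 78. This is a separate error, but it means that 80, 0.40 and 80% power do not fit together even for parallel groups. The product 80 × 2 × 4 = 640 is correct.

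**Step 2: power of 80 versus 80.** SE = √(2/80) = 0.158. Then 0.40/0.158 = 2.53 and 2.53 − 1.96 = 0.57, so power is 71.6% (71.0% by noncentral t). The effect detectable with 80% power is 2.802 × 0.158 = 0.44.

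**Step 3: crossover with 160 per profession.** SE = √(2(1 − rho)/160). Power is by noncentral t with 158 df; the detectable effect is 2.802 × SE; the number needed is 98.1 × (1 − rho), rounded up.

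| rho (assumed) | SE | Power at 0.40 | Effect detectable with 80% power | Number per profession for 80% power at 0.40 |
|---|---|---|---|---|
| 0 | 0.112 | 94.5% | 0.31 | 99 |
| 0.2 | 0.100 | 97.8% | 0.28 | 79 |
| 0.5 | 0.079 | 99.9% | 0.22 | 50 |
| 0.8 | 0.050 | >99.9% | 0.14 | 20 |

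The t distribution raises the numbers in the last column by 2 or 3. None of them reaches 160.

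**Step 4: difference in the PUSH effect between two professions.** SE = √2 × √(2(1 − rho)/160), which is 0.158, 0.112 and 0.071 at rho 0, 0.5 and 0.8. The difference detectable with 80% power is 2.802 × SE = 0.44, 0.31 and 0.20. The article states no target for this contrast. Purely as an illustration, a difference of 0.40 would have power of about 71%, 95% and over 99%.

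**Step 5: sensitivity to carryover.** Suppose half of a 0.40 effect (0.20) persists into the PULL period of those who had PUSH first. The crossover contrast then estimates 0.40 − 0.20/2 = 0.30. At rho 0, 0.30/0.112 = 2.68 and 2.68 − 1.96 = 0.72, so power is about 76%. The figures in step 3 therefore depend on the no-carryover assumption.

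**The case against.** The strongest reply is that the error is in the safe direction. Without carryover the crossover has at least 94% power at 0.40 within each profession, and no change in recruitment or conduct follows. That stands, and it limits the point to a misstated calculation. A reader might infer that the trial is underpowered for PUSH + PULL versus PULL; the figures show the opposite.

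Second, independent-group sizing has legitimate uses here. The article says that its calculation also serves comparisons between professions. Differences between professions at baseline, or between arms at month 9, are between-person, and pairing does not help them. Methods/design names incomplete wash-out as the main drawback and plans a test for order effects, so a basis that does not rely on pairing could be defended. This too stands in part. But the article does not give it as the reason, and a first-period comparison of 80 versus 80 within a profession would have about 71% power at 0.40, not 80%.

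Third, a reader might infer that the sizing contradicts the mixed model. The text is less clear than that. The same section classes intervention as a between-participant variable and plans comparisons of the arms at single time points. That labelling is awkward for a crossover, but it does not show that the sample-size basis conflicts with the analysis section.

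Fourth, a reader might infer that the sizing basis decides whether the profession-by-intervention question can be answered. It does not. Power for that question depends on the data and the model, whichever formula produced 640.

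Finally, rho and the absence of carryover are assumptions, and a condensed article may leave rho to a fuller document. That is why the replacement figures are a range. It does not rescue the multiplication by two, which is printed.

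**Conclusion.** The point holds in a limited form. The article sizes the PUSH + PULL versus PULL comparison as two independent groups of 80 per profession, although all 160 receive both conditions. The stated combination of 0.40, 80% power and 80 per group fits neither basis: it is about 71% for two groups of 80, and at least 94% for the crossover at any rho of 0 or more. For the crossover, the detectable effect is about 0.31 SD or smaller within a profession, not 0.40. These crossover figures assume no carryover, a matter on which Methods/design itself is cautious.

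The error is conservative for the crossover contrast. It gives no reason to recruit more clinicians. It also gives no reason to recruit fewer, because between-person comparisons and any first-period analysis still draw on the full number.

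**What to change.** Keep the enrolment target and rewrite the sample-size paragraph:

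- State 160 participants per profession, each contributing both six-month periods, with variance of the treatment contrast 2(1 − rho)/160 in units of the squared SD.
- Give the assumed rho as a range and state the no-carryover assumption. The baseline and month 3 questionnaire scores and the run-in usage data can inform rho.
- Report the resulting detectable PUSH + PULL versus PULL effect in each profession (about 0.31, 0.22 and 0.14 SD at rho 0, 0.5 and 0.8).
- Report the power for the profession-by-intervention contrast, with a stated target difference.
- Label the independent-group figure (about 71% at 0.40 with 80 per group) as applying only to between-person comparisons within a profession, such as a first-period or month 9 comparison of arms.
- Print 0.80 as power, not as Type II error.

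The cost is a short calculation and a reworded paragraph. The one drawback is that the result must be given as a range, because it depends on rho and on limited carryover.

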### Proposed methods for protecting against other sources of bias

#### Control over eligibility violations

Participants will complete a baseline screen with the study research assistant, which will be independently reviewed by a trainee for violations. These will be reported (as a protocol diligence indicator), but no participants will be removed. No further rechecks of eligibility or exclusions will be included after this screening.

#### Control of biases through blinding

We have attempted to create a blinded control by creating a similar front-face to the website and blinding participants to the nature of the difference in the two resources (push versus pull), although we acknowledge differences will become apparent to users. Since usage data are embedded and automated, they are not influenced by data collectors or social bias. Research assistants and data analysts will be blinded to group allocation for the duration of the study and data analysis. After crossover, subjects will be aware of the difference and, therefore, no longer be blinded. Thus, the overall potential for bias due to lack of blinding has been minimized.

#### Control of contamination and co-intervention

Inside the study, participant crossovers are impossible since we control access to the intervention. Contamination that happens by participants accessing open access content for physicians by signing up under an alias for service is possible, but not probable. As part of enrollment, we will ask participants to refrain from using any new evidence access tools/services or EBP training during the study trial and will re-evaluate their reports of services used at the end of each intervention cycle. Co-intervention will be discouraged, including attendance at intensive EBP training (although we expect that routine exposure in settings is neither controllable nor a concern since these pre-existing efforts have not been effective).

